## Abstract

**Background:**

In patients with septic shock, the presence of an elevated heart rate (HR) after fluid resuscitation marks a subgroup of patients with a particularly poor prognosis. Several studies have shown that HR control in this population is safe and can potentially improve outcomes. However, all were conducted in a single-center setting. The aim of this multicenter study is to demonstrate that administration of the highly beta1-selective and ultrashort-acting beta blocker landiolol in patients with septic shock and persistent tachycardia (HR ≥ 95 beats per minute [bpm]) is effective in reducing and maintaining HR without increasing vasopressor requirements.

**Methods:**

A phase IV, multicenter, prospective, randomized, open-label, controlled study is being conducted. The study will enroll a total of 200 patients with septic shock as defined by The Third International Consensus Definitions for Sepsis and Septic Shock criteria and tachycardia (HR ≥ 95 bpm) despite a hemodynamic optimization period of 24–36 h. Patients are randomized (1:1) to receive either standard treatment (according to the Surviving Sepsis Campaign Guidelines 2016) and continuous landiolol infusion to reach a target HR of 80–94 bpm or standard treatment alone. The primary endpoint is HR response (HR 80–94 bpm), the maintenance thereof, and the absence of increased vasopressor requirements during the first 24 h after initiating treatment.

**Discussion:**

Despite recent studies, the role of beta blockers in the treatment of patients with septic shock remains unclear. This study will investigate whether HR control using landiolol is safe, feasible, and effective, and further enhance the understanding of beta blockade in patients with septic shock.

**Trial registration:**

EU Clinical Trials Register; EudraCT, 2017-002138-22. Registered on 8 August 2017.

**Electronic supplementary material:**

The online version of this article (10.1186/s13063-018-3024-6) contains supplementary material, which is available to authorized users.

## Background

In the early phase of septic shock, overwhelming inflammation leads to vasodilation and capillary leakage, which decreases cardiac output due to both absolute and relative hypovolemia [1–3]. These alterations trigger massive sympathetic activation in the attempt to maintain vital organ perfusion. Tachycardia and vasoconstriction are the hallmarks of this activation and compensate for systemic vasodilatation [4]. In the very early phase of the septic insult, tachycardia is the main compensatory mechanism to maintain cardiac output despite the reduction of preload. Accordingly, current sepsis guidelines recommend intravascular fluid administration as the first step to counteract hypotension [4]. Compensatory tachycardia implies preserved baroreceptor and chemoreceptor activity, thus the majority of patients with sepsis rapidly respond to volume administration with a reduction of tachycardia.

However, some patients with sepsis continue to have an elevated heart rate (HR) despite adequate fluid resuscitation. This elevated HR reflects sympathetic overstimulation resulting from dysregulation of the autonomic nervous system [5–12] in addition to the effect of exogenous catecholamines [7].

Elevated HR has been associated with a poor outcome, but it is unclear whether it is a surrogate of disease severity or whether it plays a pathophysiological role that could be treated to improve patient outcomes [13–16].

Beta-blockers are potential candidates to control HR and numerous animal models provide a rationale for their use during sepsis [17–24]. Despite concerns of hemodynamic decompensation, recent clinical studies using esmolol in patients with sepsis [10, 25–34] suggest that control of HR can be safely achieved with beta1-selective beta-blockers. These studies reported a decrease in HR with limited reduction of cardiac output, improved stroke volume and lactate levels, and stabilization or improvement of organ dysfunction [10, 28–30, 32]. Furthermore, the combined use of beta-blockers and vasopressors appears to be safe and does not appear to increase the need for vasopressor support or impair microcirculation [26, 27, 34]. However, all of the previously reported studies were conducted in single centers with relatively small sample sizes and only one study included a Caucasian population.

Landiolol, the beta-blocker used in our study, is a highly beta1-selective, ultrashort-acting beta-blocker that could be ideally suited for the treatment of critically ill patients due to its limited hypotensive effect [35–38].

The aim of this multicenter, prospective, controlled study is to demonstrate that the administration of the ultrashort-acting beta-blocker landiolol in patients with septic shock and persistent tachycardia (HR ≥ 95 beats per minutes [bpm]) is effective in reducing and maintaining HR without increasing vasopressor requirements.

## Methods/Design

### Study design and objective

This is a phase IV, multicenter, prospective, randomized, open-label, controlled study on landiolol in a septic shock population (as defined by The Third International Consensus Definitions for Sepsis and Septic Shock criteria [39]) hospitalized in an intensive care unit (ICU). The study duration is expected to be 24 months from first patient enrolled until completion of the final visit for the last patient. Participating centers are listed in Table 1.

**Table 1 Tab1:** List of participating centers and ethics committee approvals

Participating center	PI	Central Ethics committee	Reference number	Approval date
Medical University Vienna, Department of Internal Medicine II. Division of Cardiology	[name]	Ethics Committee, Medical University Vienna	ECS 1805/2017	15 September 2017
Medical University Innsbruck, Division of Emergency Medicine and Intensive Care, Department Internal Medicine	[name]			
State Hospital Wiener Neustadt, Department of Anesthesiology, Emergency Medicine and General Intensive Care	[name], MSc			
University Hospital Greifswald, Department of Anesthesiology, Intensive Care, Emergency and Pain Medicine	[name]	Ethics Committee, University Hospital Greifswald	FFV 06/17	15 February 2018
University Hospital Munich, Department of Anesthesiology	[name]			
University Hospital Hradec Králové, Department of Anesthesiology, Resuscitation and Intensive Medicine	[name], PhD, MBA	Ethics Committee, University Hospital Hradec Králové	201801 I126M	07 November 2017
Masaryk Hospital, Department of Anesthesiology, Perioperative Medicine and Intensive Care	[name], MD, PhD, FCCM			
University Hospital La Sapienza, Department of Anesthesiology and Intensive Care	[name].	Ethics Committee, University Hospital La Sapienza	4846	08 February 2018
Azienda Ospedaliero Universitaria Pisana, Department of Anesthesiology and Resuscitation 5	[name]			
Azienda Ospedaliero Universitaria Pisana, Department of Anesthesiology and Resuscitation 6	[name]			
University School of Medicine Pisa, Department of Anesthesiology and Transplant Intensive Care Unit	[name]			
University Hospital Modena, Department of Anesthesia and Intensive Care	[name]		Approval pending	

The study objective is to compare the percentage of patients with a HR response (defined as HR within the target range of 80–94 bpm) and maintenance thereof without an increase in vasopressor requirements within the first 24 h of treatment, and to further assess efficacy and safety in the two treatment arms: standard of care treatment and landiolol (landiolol group) or standard of care treatment alone (control group).

Additional file 1 contains the completed Standard Protocol Items: Recommendations for Interventional Trials (SPIRIT) checklist.

### Study population

This study will enroll a total of 200 patients with septic shock and elevated HR (≥ 95 bpm) despite a hemodynamic optimization phase of at least 24 h but a maximum of 36 h in which they received adequate fluid resuscitation and continuous vasopressor treatment (according to the Surviving Sepsis Campaign Guidelines 2016 [40]). Detailed inclusion and exclusion criteria are displayed in Table 2.

**Table 2 Tab2:** Inclusion/exclusion criteria

Inclusion criteria 1. Informed consent 2. Age ≥ 18 years 3. Confirmed septic shock: a. Confirmed or suspected infection b. Acute increase of ≥ 2 points on SOFA Score c. Need for continuous vasopressor therapy to maintain a mean arterial pressure (MAP) of > 65 mmHg despite adequate fluid resuscitation d. Blood lactate > 2 mmol/L (18 mg/dL)^a^ 4. Tachycardia and/or tachyarrhythmia with heart rate ≥ 95 bpm 5. Norepinephrine infusion rate ≥ 0.2 μg/kg/min at the time of study inclusion 6. Patients must have undergone a hemodynamic optimization period of at least 24 h but a maximum of 36 h, during which period they received continuous vasopressor treatment and standard treatment for septic shock according to the SSCG 2016 guidelines ^a^Presence of blood lactate > 2 mmol/L (18 mg/dL) and increase of ≥ 2 points on SOFA score are mandatory for the diagnosis of septic shock, but must not necessarily be present at the time of study inclusion Exclusion criteria: 1. Any form of compensatory tachycardia 2. β-blocker treatment within 72 h before randomization 3. Sick sinus syndrome, or second or third degree AV block 4. Patients with any form of cardiac pacing 5. A known serious cardiovascular condition such as ischemic stroke or transient ischemic attack within the last six months, or pre-existing heart failure NYHA class III or IV 6. Cardiogenic shock 7. MAP < 65 mmHg 8. Known pulmonary hypertension 9. Known terminal illness other than septic shock with expected patient’s survival < 28 days 10. Known presence of an advanced condition to withhold life-sustaining treatment 11. Patients for whom a “Do Not Resuscitate” (DNR) order exists 12. Known sensitivity to any component of the study medication (e.g. landiolol, mannitol) 13. Participation in a clinical drug trial within 30 days before randomization 14. Any condition that, in the investigator’s opinion, makes the individual unsuitable for study participation (to be documented) 15. Pregnant or breast-feeding patients 16. Untreated pheochromocytoma	

*NYHA* New York Heart Association

### Randomization, blinding, and treatment allocation

Patients fulfilling the selection criteria are randomized in a 1:1 ratio to one of the two groups (landiolol or control) after informed consent, as required by local law, has been obtained. The presence of atrial fibrillation in the hemodynamic optimization period is used as a stratification factor for randomization. As this is an open label study, investigators and other study personnel will not be blinded to the treatment.

### Study drug

Lyophilized landiolol hydrochloride 300 mg (Rapibloc Lyo, 300 mg) is to be reconstituted in 50 mL of 0.9% NaCl to a concentration of 6 mg/mL before use.

### Treatments

#### Landiolol group

Patients in the landiolol group begin continuous infusion with landiolol within 2 h after randomization at a starting dose of 1 mcg/kg/min. The dose is to be progressively increased at increments of 1 mcg/kg/min to a maximum of 40 mcg/kg/min at intervals of at least 20 min to obtain and maintain a HR of 80–94 bpm. Landiolol must be infused continuously to maintain the target HR until one the following events occurs: discontinuation of vasopressor infusion; death; a serious adverse event (AE) attributable to the study drug that necessitates study drug discontinuation as determined by the investigator; patient discharge from the ICU; or day 28 of study participation.

#### Control group

Patients in the control group receive standard of care treatment according to the Surviving Sepsis Campaign Guidelines 2016 [40], which does not specify a target for HR control. Patients in the control group are to be withdrawn from the study if they receive beta-blocker treatment.

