### Sample size

Sample size estimation is based upon the assumption that 60% of patients in the landiolol group reach the primary endpoint versus 40% of patients in the control group. The sample size of 200 patients will provide 80% power to demonstrate a statistically significant difference (upon standard level alpha = 0.05) between the treatment groups using a Chi-square test. The sample size in the study by Morelli et al. [10] was adequate considering that to detect a 20% change in HR with a power of 80% at a level of significance of alpha = 0.05, 64 patients per group would have been required. In order to detect the binary primary endpoint of our study an additional 36 patients per group are required.

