### Statistical analysis

The hypothesis that Group L is superior to Group C in proportion of patients who reached the primary endpoint will be demonstrated if the lower limit of the two-sided 95% Newcombe confidence interval of difference pL-pC is above zero, where pL and pC are percentages of patients who reached the primary endpoint in Group L and Group C, respectively. *P* values based on Cochran–Mantel–Haenszel (according to SAS® terminology) will be presented together with the confidence intervals to evaluate statistical significance of association between treatment group and outcome after adjustment for the stratification group. For the purpose of exploratory analysis, the individual criteria of the primary endpoint, heart rate response (i.e. HR = 80–94 bpm) reached (also defined as secondary endpoint), heart rate response reached and maintained and no increase in vasopressor requirements during the first 24 h, will be compared separately between treatment groups. Additional subgroup and sensitivity analyses will have exploratory character and will be defined in all details in the SAP.

Secondary endpoints with continuous, ordinal, and binary variables measured at multiple time-points will be analyzed as longitudinal data by linear, ordinal logistic, logistic, or log-binomial regression models with repeated measures. Covariates used in the models will be (but not limited to) treatment, visit, stratification group, and interaction treatment/visit. For continuous variables baseline value of the outcome variable will be a covariate as well. Distribution of data and a feasibility check of planned analyses will be performed before finalization of SAP and alternative statistical methods will be defined if assumptions on the application of the planned methods are not met (e.g. ln-transformation of data, non-parametric method, or other alternative way). ICU mortality and 28-day mortality will be analyzed using the same methods as for the primary endpoint. Duration of ICU stay and duration of hospital stay (in survivors/non-survivors) will be analyzed as time-to-event data (using Kaplan–Meier curve and using log-rank test or Wilcoxon test and/or proportional hazards regression model if appropriate).

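### Only control patients are withdrawn from the study on receiving a beta-blocker, with no stated further follow-up: a risk of bias of unknown size and direction, chiefly in mortality, length of stay and SOFA

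*Protocol article*

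**What the plan says.** Under Control group, the protocol article sets this rule: "Patients in the control group are to be withdrawn from the study if they receive beta-blocker treatment". The withdrawal is from the study, not from a treatment. No time limit is attached, and nothing is said about continued assessment or vital status afterwards.

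The Landiolol group section has no counterpart. It lists only events that end the infusion: "Landiolol must be infused continuously to maintain the target HR until one the following events occurs: discontinuation of vasopressor infusion; death", followed by a drug-related serious adverse event that requires stopping, ICU discharge and day 28. None of these is described as leaving the study.

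The section on randomisation and blinding states: "As this is an open label study, investigators and other study personnel will not be blinded to the treatment". Whoever gives the beta-blocker therefore knows the arm.

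The primary endpoint (Endpoints, Table 3) covers the first 24 h after treatment start. The secondary endpoints include 28-day mortality, ICU mortality, ICU and hospital stay, and SOFA on set days up to day 28. For mortality the plan is: "ICU mortality and 28-day mortality will be analyzed using the same methods as for the primary endpoint". That means a comparison of proportions.

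The Sample size section assumes "60% of patients in the landiolol group reach the primary endpoint versus 40% of patients in the control group" and concludes: "The sample size of 200 patients will provide 80% power to demonstrate a statistically significant difference". It states no withdrawal rate and no allowance for one.

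**The concern.** A patient should not leave a randomised comparison because of a treatment decision taken after randomisation. Here the departure is written into the protocol, for one arm only.

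Every patient enters with a heart rate of at least 95 bpm, and tachyarrhythmia qualifies, so some beta-blocker use among controls is foreseeable. The controls who receive one are unlikely to be a random sample. Early on they may be those whose tachycardia persists; later they may be patients who are recovering. The first kind of removal would raise the response rate of the remaining controls, and the second would raise their mortality.

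The late endpoints are the most exposed, because a beta-blocker on, say, day 10 triggers the rule as readily as one in hour 10. An analysis plan can define analysis sets and imputation, but it cannot supply a day-28 status that was never collected.

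**Working it through.** **Inputs from the article.** 200 patients randomised 1:1, so 100 per arm; response 60% with landiolol and 40% in control; alpha 0.05, chi-square test, 80% power (Sample size). Superiority is claimed if the lower limit of the two-sided 95% Newcombe interval exceeds zero (Statistical analysis), which is a nominal 2.5% in landiolol's favour.

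**Inputs not in the article, so assumed.** w = share of controls withdrawn within 24 h and excluded from the analysis; q = share of those who would have reached the primary endpoint. Mortality figures below are also assumed.

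**Step 1. The plan's own figure.** With the pooled chi-square formula,
n per arm = [1.960 × √(2 × 0.5 × 0.5) + 0.842 × √(0.6 × 0.4 + 0.4 × 0.6)]² / 0.20² = 96.9, so 97.
With 100 per arm, power is 81.2% by the normal approximation and 82.6% by exact binomial enumeration of the Newcombe rule. The stated 80% reproduces, with 3 patients per arm to spare.

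**Step 2. Random loss (q = 0.40).** Only the control sample size shrinks. Exact Newcombe power:

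| Controls lost | Power |
|---|---|
| 5% | 79.9% |
| 10% | 79.5% |
| 20% | 76.9% |

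**Step 3. Selective loss.** The response rate among remaining controls is (0.40 − w × q) / (1 − w). If none of the withdrawn would have responded (q = 0):

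| w | Remaining control rate | Exact power |
|---|---|---|
| 5% | 0.40/0.95 = 42.1% | 70.4% |
| 10% | 0.40/0.90 = 44.4% | 58.3% |
| 20% | 0.40/0.80 = 50.0% | 27.0% |

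The effect can also go the other way. With w = 10% and q = 0.80, the remaining control rate is (0.40 − 0.08)/0.90 = 35.6%, the apparent difference is 24.4 points and power is 93%.

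**Step 4. No true effect (40% in both arms), w = 10%.** Exact probability of claiming superiority, nominal 2.5%:

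| q | Withdrawn controls excluded | Counted as non-responders |
|---|---|---|
| 0 | 0.5% | 2.6% |
| 0.40 | 2.6% | 8.4% |
| 0.80 | 9.3% | 21.6% |

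The last column bears on the choice of fix.

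**Step 5. Mortality.** Assume true control mortality of 40%, a share w withdrawn at any time and excluded, and mortality m among them. The remaining controls show (0.40 − w × m)/(1 − w).

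| w | m = 20% | m = 60% |
|---|---|---|
| 10% | 0.38/0.90 = 42.2% | 0.34/0.90 = 37.8% |
| 20% | 0.36/0.80 = 45.0% | 0.28/0.80 = 35.0% |

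The sign depends on the prognosis of the withdrawn, which cannot be known if follow-up stops.

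**The case against.** A reader might infer that the rule does bias the primary and mortality results and does cost the trial its 80% power. The article does not support that, for these reasons:

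- **Frequency and prognosis are unknown.** The article gives no number, timing or prognosis for controls given a beta-blocker. Its standard of care sets no heart-rate target, and inclusion requires norepinephrine of at least 0.2 μg/kg/min, so use within 24 h may be rare. With two controls lost, exact power is 82.0% if the loss is random and 78.8% if both would have been non-responders.
- **Exclusion from the analysis is not stated.** The article does not say that collected data are discarded or that vital status is not sought. The full protocol or analysis plan may settle this.
- **Direction is not fixed.** Removing would-be non-responders works against landiolol and lowers the false-claim rate. The opposite direction needs withdrawn controls who would mostly have responded.
- **Mortality is secondary.** The Statistical analysis section rules out confirmatory conclusions from secondary endpoints.
- **Some asymmetry is inherent.** Landiolol is itself a beta-blocker, so the same rule could not apply literally to that arm.

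All of this stands against a claim of proven bias or proven loss of power. It does not remove the point. The rule is stated rather than omitted, it says withdrawal from the study, and no later document can recover outcomes that were not collected. The inherent asymmetry explains why beta-blocker use is recorded differently in the two arms; it does not explain why one arm's patients should stop being followed. Non-confirmatory mortality results will still be read, especially in septic shock.

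**Conclusion.** The concern holds as a risk. A one-arm rule, triggered by an unblinded decision after randomisation and without a time limit, exposes the comparison to bias of unknown size and direction. The exposure is greatest for 28-day and ICU mortality, length of stay and SOFA. The primary endpoint is directly exposed only to beta-blocker use within 24 h, unless patients withdrawn later are also dropped from its analysis set.

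The sample size is sound on its own terms, and loss of numbers alone is a minor matter. Selection is what can hurt: at an assumed 10% of controls excluded, power could be as low as 58%, and the false-claim rate could lie between 0.5% and 9.3% for q between 0 and 0.80. These figures rest on assumed values of w and q and on exclusion from the analysis, none of which the article states. They show how sensitive the result is and do not predict it.

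**What to change.** Replace study withdrawal with wording to this effect: beta-blocker use in the control group is recorded as a protocol deviation, with date and time; the patient stays in the study; all scheduled assessments and vital status are collected to day 28; and the patient is analysed in the arm assigned at randomisation.

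For the primary endpoint, mortality and length of stay, the main analysis should use observed outcomes regardless of beta-blocker use. Counting controls given a beta-blocker within 24 h as non-responders belongs in a sensitivity analysis only. As the main analysis in an open-label trial, it would let an unblinded decision create control failures (false-claim rate 2.6% to 21.6% in the last column of step 4).

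The cost is a short protocol amendment, a matching line in the analysis plan, and continued routine data collection for the controls concerned. Concomitant medication is already documented throughout the study. The downside is that some contamination remains in the control arm. Enrolment began on 24 February 2018 (Trial status), so the change should be made soon.

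This concerns follow-up and analysis only, not whether any patient should receive a beta-blocker.
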